### Statistical analysis

Analysis of the primary outcomes will be done on an intention-to-treat basis. For each endpoint, a linear regression will be used to estimate differences in the cluster-level prevalence of the indicator at follow-up. The intervention and control clusters in the six study sites with only the digital interactive counselling will be compared in one analysis. A separate analysis will compare intervention and control clusters in the two study sites which also include the community conversations component. Any indicators unbalanced at baseline will be included as covariates. The Shapiro–Wilk normality test will be used to test for non-normality of the model residuals, and standard non-parametric tests (e.g. Mann–Whitney rank-sum test) will be used in case of non-normality. Effect sizes will be reported with 95% confidence intervals and results will be considered significant if *P* < 0.05. Data will be analyzed using STATA version 15.

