
### Inclusion and exclusion criteria

A total of 1200 women will be considered eligible if: (1) they are aged 18–24 years; (2) they live in the intervention cluster (see below) in one of the eight study sites in Manicaland province; and (3) they expect to be resident there for the duration of the study. Participants will be excluded if they test positive for HIV at baseline or self-report taking PrEP at baseline. To avoid indirect disclosure of the status of HIV-positive individuals, a random sample of 90% of otherwise eligible HIV-negative women will be selected to participate in the intervention.

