### Randomization/masking

In each study site, community leaders will first be contacted and clearance will be sought to carry out activities. In addition, community meetings will be organized to introduce the activities before the start of any procedures. Within each of the eight study sites (including the two sites with the additional CC intervention component), detailed site maps will be used to create two matched clusters of villages based on socioeconomic characteristics and factors such as distances to trading centers, major roads, and health centers. Clusters within a site will be randomly allocated to intervention or control using a simple coin toss process. Thus, all eight sites will contain two clusters each (intervention and control). Young women in intervention clusters will receive the interactive intervention (and in two sites, CCs will also be implemented). Young women in the control villages will receive no intervention and will be followed up for measurement of outcomes at six months. Participants will not be masked for the intervention they receive due to cluster level randomization and the nature of the intervention. Study interventions and measurements will occur in separate locations and time points thus facilitating the blinding of outcomes assessors.

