### Primary and secondary outcomes

HIV prevention cascades (HPCs) have been proposed to facilitate identification of gaps in implementation of primary HIV prevention methods, understanding of the reasons for these gaps, and identification and evaluation of promising interventions to address the gaps [25, 26]. The population of HPCs using existing study data motivated the selection of some of the outcomes for this study. While no prior measurements were available to populate a HPC specifically for PrEP, analyses of the HPC for existing prevention methods among AGYW in the study population [25, 26] found major gaps in perceptions about personal risk of HIV infection.

The primary outcome for the study will be the proportion of women taking up PrEP within six months measured via biomarkers of ARV presence from DBS and triangulated with self-reports and clinic data. The secondary outcomes will be risk perception measured at baseline and in a follow-up survey at six months, and self-reported change in sexual behavior between baseline and follow-up surveys.

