### Sample size estimates

It is estimated that a sample size of 600 participants per arm would be necessary to detect meaningful minimum effect sizes (around 20%) for the primary endpoint (PrEP uptake), with 80% power (*α* = 0.005). Survey data from the study sites in 2012–2013 were used to calculate mean cluster size, coefficient of variation in cluster size (0.15 for women), and the intra-cluster correlation coefficient (ICC) (0.04 using HIV incidence as the outcome). Baseline prevalence estimates of endpoint indicators were assumed to be 10% for PrEP. It was also assumed that 80% of eligible participants consent to participate and that 80% of these are followed up at six months (mean cluster size of 48). The exploratory nature of the intervention combining interactive counselling and community engagement means that we have chosen to use only two clusters for this intervention as this allows greater power to detect the effect without the community-level intervention. Nevertheless, in the two sites with the combined intervention, the study is powered to detect large impacts (effect size difference = 40%) on the outcome indicators. As a further consequence, there is not sufficient power to examine the interaction of the effect sizes with and without the addition of the community-level intervention.

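### The uncapped, imbalance-driven covariate rule cannot be carried by the four-cluster analysis, erodes the twelve-cluster one, and leaves baseline risk perception to enter only by chance

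*Protocol article*

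**What the plan says.** Under Statistical analysis, for each endpoint, "a linear regression will be used to estimate differences in the cluster-level prevalence of the indicator at follow-up". The model is fitted twice. First: "The intervention and control clusters in the six study sites with only the digital interactive counselling will be compared in one analysis". Second: "A separate analysis will compare intervention and control clusters in the two study sites which also include the community conversations component". The covariate rule follows: "Any indicators unbalanced at baseline will be included as covariates". The section promises effect sizes with 95% confidence intervals and a 0.05 significance threshold.

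Randomization/masking gives each of the eight sites one intervention and one control cluster. Primary and secondary outcomes lists the secondary outcomes as "risk perception measured at baseline and in a follow-up survey at six months, and self-reported change in sexual behavior between baseline and follow-up surveys". Under Inclusion and exclusion criteria, women who "self-report taking PrEP at baseline" are excluded, so PrEP uptake has no useful baseline level to adjust for.

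**The concern.** A regression on cluster values has as many observations as clusters, however many women are surveyed. Each covariate costs one of very few residual df, and this rule sets no limit on how many enter. It is also settled by the data: the model is unknown until baseline differences have been inspected, and chance imbalance is common with few clusters.

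The rule also selects on the wrong property. What makes a covariate useful is that it predicts the outcome, not that it happens to differ between arms. For risk perception the obvious candidate is the cluster's own baseline level, which is collected anyway but enters the follow-up model only if it looks unbalanced.

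At stake are whether the two-site effect can be given any interval at all, some precision in the main comparison, and a model fixed in advance.

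**Working it through.** **Inputs.** From Sample size estimates: 10% reference level, effects of about 20% and (combined intervention) 40%, ICC 0.04, mean cluster size 48, coefficient of variation of cluster size 0.15, 80% power, α = 0.005, 80% consent and 80% follow-up. From Statistical analysis: significance at 0.05. The effects are read as percentage points, which the first step supports.

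**1. The plan's own figure.** For 10% versus 30%, two-sided α 0.005:
- n = (2.807 + 0.842)² × (0.1×0.9 + 0.3×0.7) / 0.2² = 99.8 per arm.
- Design effect 1 + 47×0.04 = 2.88, so 287.6 evaluable women, against 6 × 48 = 288.
- Divided by 0.8×0.8 = 0.64 and scaled from six to eight sites: 287.6 / 0.64 × 8/6 = 599, against 600 stated.

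With the variation in cluster size the design effect is 1 + (1.0225×48 − 1)×0.04 = 2.923 and the total is 608. The figure is reproduced. It uses normal quantiles and allows nothing for few residual df or for covariates.

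**2. Residual df.** df = clusters − 2 − k, with k covariates (intercept and arm take two).
- Six sites: 12 − 2 − k = 10 − k, zero only at k = 10.
- Two sites: 4 − 2 − k = 2 − k, zero at k = 2.

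If matched-pair terms were added (the article does not mention them), the starting points would be 5 and 1 df.

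**3. Power at α = 0.05.** Noncentral t, design effect 2.923, residual variance unchanged by the covariates (uninformative).

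Six sites, 10% versus 30%: SE = √(0.30 × 2.923 / 288) = 0.0552; 0.2 / 0.0552 = 3.62.

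| Covariates | df | Critical t | Power |
|---|---|---|---|
| 0 | 10 | 2.23 | 0.90 |
| 2 | 8 | 2.31 | 0.89 |
| 5 | 5 | 2.57 | 0.82 |
| 7 | 3 | 3.18 | 0.68 |

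Two sites, 10% versus 50%: SE = √(0.34 × 2.923 / 96) = 0.102; 0.4 / 0.102 = 3.93.

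| Covariates | df | Critical t | Power |
|---|---|---|---|
| 0 | 2 | 4.30 | 0.55 |
| 1 | 1 | 12.71 | 0.24 |
| 2 | 0 | none | no SE, CI or P |

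**4. How often an indicator is flagged.** The article gives no criterion, so a range is shown. For an indicator with no true difference, ICC 0.04 and 48 per cluster, the standardised difference has SE √(2 × 2.923 / (48c)), with c clusters per arm.

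| Analysis | SE | P(flag), threshold 0.25 | P(flag), threshold 0.1 |
|---|---|---|---|
| Six sites (c = 6) | 0.142 | 8% | 48% |
| Two sites (c = 2) | 0.247 | 31% | 69% |

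In the two-site analysis, if there were only two candidate indicators and they were independent, the chance that both are flagged is 0.311² = 10% to 0.685² = 47%.

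A separate simulation assumed 10 independent candidates and 75 women per cluster, without pair terms. With individual-level 5% tests ignoring clustering, no residual df remained in 90% of two-site and 0% of six-site replicates. With cluster-level 5% tests the shares were 10% and 0%. Where models could be fitted often enough to judge, type I error stayed near 0.05.

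**5. Baseline values.** Risk perception is measured at both times, while the analysis models the follow-up level, so its baseline enters only through the imbalance rule. Sexual behaviour is defined as a change, which uses the baseline by construction, yet the analysis text refers to the level at follow-up. The two sections disagree for that outcome.

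**The case against.** The best reply has four parts.

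**The main comparison is not broken.** This stands. A reader might infer that the rule uses up the df in both analyses. With 12 clusters that takes ten covariates, or five with pair terms. The article uses the word indicator mostly for endpoints, so the candidates may be few; two flagged covariates leave 8 df and power 0.89.

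**The flag rates rest on assumptions.** This also stands, which is why a range is given. The problem does not vanish within it: with only two candidates, the two-site model still loses all residual df in roughly 10% to 47% of cases under thresholds of 0.25 to 0.1.

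**The two-site comparison is exploratory and weak in any case.** True: the article calls the combined intervention exploratory, and power is about 0.55 with no covariates. But the article claims power for a 40-point effect there and promises confidence intervals, and the rule can remove the interval altogether.

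**This is detail for the analysis plan.** The criterion and the candidate list could be left to it. The sentence itself is not an omission: it is an unconditional instruction, and a plan with a fixed covariate set would contradict it.

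Two further readings are tempting and unsupported. One is that data-driven selection inflates type I error; the simulation does not show this. The other is that the baseline of every secondary outcome is used only by chance. That fits risk perception. It fits sexual behaviour only if the follow-up level is what is analysed.

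**Conclusion.** The concern holds in limited form. The covariate rule is stated, uncapped and data-driven, and it suits neither regression.

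- **Two sites:** one covariate takes power for 40 points from 0.55 to 0.24, and two make inference impossible.
- **Six sites:** the harm is gradual, from 0.90 to 0.89 with two uninformative covariates and 0.82 with five.
- **Risk perception:** adjustment for its own baseline is left to chance.
- **Sexual behaviour:** the outcome definition and the analysis text need reconciling.

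The df counts follow from the article alone. The power figures assume ICC 0.04, 48 women per cluster, percentage-point effects and unchanged residual variance. The flag rates also need an assumed threshold. The harm is lost precision, a possibly inestimable model and a model not fixed in advance; it is not a demonstrated false-positive problem. The change is worth making before analysis.

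**What to change.** Replace the imbalance sentence with a small covariate set that applies whatever imbalance is seen.

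- **Six-site analysis, risk perception:** always include the cluster's baseline level of the same indicator. Do the same for sexual behaviour if its follow-up level is analysed.
- **Six-site analysis, PrEP uptake:** no imbalance-selected covariates.
- **Individual-level covariates such as age, if wanted:** name them in advance, fit them in a first-stage individual-level model without arm, and compare cluster residuals. This spends no cluster-level df.
- **Two-site analysis:** no covariates, or report it descriptively.
- **Sexual behaviour:** state whether change or follow-up level is analysed, and use the same definition in both sections.
- State the residual df of each model.

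The cost is wording and one df in the six-site secondary analyses (10 to 9). On the 20-point example that moves power only from 0.903 to 0.896 even if the covariate explains nothing. The baseline surveys are already planned, so no new data are needed.

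Whether to add a site or pair term is a separate choice that this fix does not make. It would cost a further 5 df in the six-site analysis (12 − 2 − 5 − 1 = 4 with a baseline term). In the two-site analysis a site term plus a baseline term would leave 4 − 2 − 1 − 1 = 0, so that pairing must not be carried over there.

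### A normality test on 12 or 4 cluster residuals can replace the adjusted regression with an unadjusted rank test, which in the two-site analysis can never reach P < 0.05

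*Protocol article*

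**What the plan says.** All the rules stand in one paragraph of the protocol article, under Statistical analysis.

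- Model: "a linear regression will be used to estimate differences in the cluster-level prevalence of the indicator at follow-up".
- Two comparisons: "The intervention and control clusters in the six study sites with only the digital interactive counselling will be compared in one analysis", and "A separate analysis will compare intervention and control clusters in the two study sites" that add community conversations.
- Adjustment: "Any indicators unbalanced at baseline will be included as covariates".
- Pre-test: "The Shapiro–Wilk normality test will be used to test for non-normality of the model residuals".
- Fallback: "standard non-parametric tests (e.g. Mann–Whitney rank-sum test) will be used in case of non-normality".
- Reporting: "Effect sizes will be reported with 95% confidence intervals", with significance at P < 0.05.

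The Randomization/masking section fixes the number of clusters: "Thus, all eight sites will contain two clusters each (intervention and control"). The paragraph makes no exception for the two-site analysis. It does not say how covariates carry into the fallback, and it does not say that the regression estimate is dropped.

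**The concern.** The outcome data decide, endpoint by endpoint, which test determines significance, and the deciding test has 12 or 4 values to work with. The fallback named as the example is a two-sample rank test. It takes no covariates, so the adjustment rule lapses in the test that decides significance. If the regression estimate and interval are still reported, the P value and the interval come from different analyses and may point in opposite directions. With two clusters per arm, a rank test may be unable to reach the 0.05 threshold at all. At stake are the interpretability of any endpoint that triggers the switch and the usability of the two-site comparison.

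**Working it through.** **Inputs.** From Sample size estimates: uptake 10%, ICC 0.04, cluster-size CV 0.15, mean analysed cluster size 48, effects of about 20% and, in the two sites, 40% (read as percentage points), α = 0.005. From Statistical analysis: significance at P < 0.05. Assumed because not stated: Shapiro–Wilk judged at 5%, two-sided tests, and cluster-level correlations between a baseline covariate and the outcome of 0.3 to 0.7.

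**The plan's own figures.** Cluster size: 600 × 0.8 × 0.8 / 8 = 48, as stated. Design effect: 1 + (48 − 1) × 0.04 = 2.88. Two-site effective size per arm: 2 × 48 / 2.88 = 33.3. For 10% v 50% at two-sided α = 0.005 with pooled null variance, the null SE is √(2 × 0.3 × 0.7 / 33.3) = 0.112 and the alternative SE is √((0.09 + 0.25) / 33.3) = 0.101. Then z = (0.40 − 2.807 × 0.112) / 0.101 ≈ 0.84, which gives 80% power. The 40% claim is reproduced, so the protocol does expect the two-site comparison to be able to show significance.

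**Residual counts.** The model has one residual per cluster: 6 × 2 = 12 and 2 × 2 = 4.

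**What the pre-test detects with 12 residuals.** Beta-binomial clusters were simulated with the inputs above, unpaired, with a t test on cluster proportions and Shapiro–Wilk on arm-centred residuals.

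| Uptake | Pre-test rejects | Regression significant | P value and interval disagree, given rejection |
|---|---|---|---|
| 10% v 10% | about 14% | about 4.6% | 2–3% |
| 10% v 30% | about 8% | about 91% | about 7–9% |

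Under the null the regression holds its level, so the 14% of rejections do not mark a failing test. They reflect proportions lying near zero. At 10% v 30% the disagreement affects about 0.08 × 0.08 ≈ 0.6% of all trials. If control uptake were lower than the protocol assumes, the pre-test would reject more often: in about one third of null trials at 5% uptake and three quarters at 2%. Those uptake levels are assumptions.

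**What it detects with 4 residuals.** With arm as the only term, each arm's two residuals are equal and opposite: +a, −a, +b, −b. The Shapiro–Wilk P value therefore depends only on the ratio of the two spreads.

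| Smaller / larger spread | 0.60 | 0.90 | 0.95 | 1.00 |
|---|---|---|---|---|
| P | 0.49 | 0.063 | 0.040 | 0.024 |

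It rejects only when the arms' spreads are nearly equal, which is where the equal-variance model fits best. With one covariate added, 4 − 3 = 1 residual degree of freedom remains. The residuals are then a fixed vector multiplied by a number, and because the statistic ignores scale and sign, the outcome data no longer influence it.

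**What the fallback can conclude.** The smallest exact two-sided rank-sum P is 2 / C(12,6) = 2/924 = 0.0022 at 6 v 6, and 2 / C(4,2) = 2/6 = 0.333 at 2 v 2. The normal approximation gives 0.121 at 2 v 2. At 10% v 50% the pre-test rejects in about 4% of two-site trials, and in roughly 62 to 64% of those the regression would have been significant. That is about 0.04 × 0.63 = 2.5% of trials.

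**False positives of the whole rule (12 clusters).** Without imbalance the two-stage rule gives 3.4 to 5.1%. For imbalance of at least 1 cluster-level SD, the SE of the difference is √(2/6) = 0.577 SD, so the cut-off is 1 / 0.577 = 1.73 SE, which about 8% of randomisations exceed. Given that imbalance in a prognostic covariate, the whole rule gives about 5 to 9%. When the pre-test also rejects, the rank test gives about 5 to 23% and the adjusted regression 1 to 4%. Both events together occur in 0.3 to 2.2% of trials.

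**The case against.** A reader might infer that the rule materially raises the trial's false-positive rate. The documents do not support that. The overall rate stays near 5%, the inflation needs two uncommon events together, and its size rests on correlations the protocol does not give. The matching of clusters is also meant to limit imbalance. Baseline imbalance in PrEP use itself cannot arise, because women who report taking PrEP at baseline are excluded. For the primary endpoint, only imbalance in other indicators matters. In the two-site comparison the exact rank-sum test has no false positives at all.

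A reader might also infer that the effect estimate is lost. The text does not say so: the regression estimate could stand beside a rank P value. At 6 v 6 a rank-based shift estimate with a 95% interval also exists. At 2 v 2 it does not, since the widest such interval covers 1 − 2/6 = 67%.

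The rank-sum test is given only as an example, and a rank test on covariate-adjusted residuals is possible. The switch is set in advance and applied by blinded analysts, so it is not selective choice. An article also leaves detail to an analysis plan.

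These points limit the harm, but the rule remains. The pre-test, the switch and the example are written into the protocol. They sit beside an adjustment rule that the named test cannot follow and a two-site claim that it cannot meet.

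**Conclusion.** The point holds as a rule that is fixed badly and should be changed. The Shapiro–Wilk test says little about whether the regression is valid: with 12 residuals it rejects in about 14% of null trials in which the regression keeps its level, and with 4 residuals it responds to near-equal spreads. When it triggers, significance is judged by a test without the required covariates, and the P value may conflict with the reported interval. In the two-site comparison the fallback can never meet P < 0.05. That last result is exact and needs no simulation assumption.

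The practical size is modest. At the design scenario the conflict touches under 1% of six-site trials, and the overall error rate is close to nominal. The simulated figures assume a 5% Shapiro–Wilk threshold, beta-binomial clusters with the protocol's ICC and no site pairing. The imbalance figures also depend on the assumed correlations.

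**What to change.** Delete the Shapiro–Wilk pre-test and the rank-sum fallback. For every endpoint, report the adjusted cluster-level regression estimate with its t-based 95% confidence interval and the P value from the same model.

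If a distribution-free check is wanted, pre-specify one for the six-site comparison only: a permutation test of the same adjusted coefficient that re-assigns arm within site, as a sensitivity P value that does not replace the estimate. There are 2^6 = 64 allocations, so the smallest two-sided P is 2/64 = 0.031. In the two-site comparison there are 2^2 = 4 allocations and the smallest P is 2/4 = 0.5. Neither a rank test nor a within-site permutation test should decide significance there.

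The cost is a change of wording and, for the optional check, a few lines of Stata. No data collection changes. The drawback is the coarse P value of the permutation check.

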## Discussion

This trial will evaluate the impact of an interactive counselling game on improving perception of HIV risk and uptake of PrEP among young women aged 18–24 years. The present study will provide reliable and high-quality estimates of the average treatment effects because it is a randomized and prospectively registered study, it masks the evaluators, and it uses an intention-to-treat approach. Sample size was calculated to provide adequate statistical power to identify possible differences in the study’s primary outcome. In addition, the six-month follow-up will allow adequate time for participants to present at clinic with referral letters for PrEP and to evaluate changes in risky sexual behavior but not be too long to measure adjustment in risk perception. Findings from this study will help determine whether interactive feedback counselling leads to uptake of HIV prevention methods such as PrEP and reduces risky sexual behavior. If successful, policymakers could consider such an intervention in school-based education campaigns or as post-HIV-testing counselling for young people.

This study has limitations. Some participants may be unable to read information presented as text, although the general literacy level in Zimbabwe is relatively high even in rural areas. Another potential limitation is the possibility of lower than expected retention rates especially among young women who may move away due to marriage or for family reasons. Any retention challenges will provide valuable information in planning for future research and intervention implementation. Other limitations of this RCT could include recruitment challenges and potential sampling bias. The eligibility, recruitment, enrolment, and retention will be closely monitored to overcome such challenges.

To reach and maintain the UNAIDS 90–90-90 goals and to achieve the Sustainable Development Goal of ending the AIDS epidemic as a public health threat by 2030, considerable expansions of HIV prevention efforts are needed. This is especially the case for AGYW who face a high risk of acquiring a lifelong incurable infection which threatens their health and wellbeing. However, while efficacious methods of HIV prevention exist, their uptake remains limited. This study will generate important knowledge to inform HIV prevention policies about the effectiveness of novel interventions to improve HIV prevention uptake, which are devised in such a way that they could be easily scaled up (e.g. as an extension to routine HIV testing and counselling services). These results will not only be applicable to Zimbabwe but also to other settings with high HIV prevalence.

